**Goal Attainment Scaling**

Goal attainment scaling is a patient-reported outcome measure. Goals are selected, and further goals are standardized to extend by which the study participant meets the chosen goals. Here, we aim to choose the attainment of physical, mental and social goals. In this scaling, goals are weighted with the importance multiplied by difficulty. Further, importance and difficulty are rated on a scale of 4, starting from 0 to 3; where 0 means not at all (important/difficult). 4 means very important/difficult, leading to the generation of scoring goals. Where -1 means the patient experiences difficulties in achieving that particular goal, while -2 will be the baseline rate. [[130](#_heading=h.488uthg)]

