| Endpoints | **Primary Endpoint:**  The frequency and type of treatment-emergent adverse events among participants treated with CBD-enriched CHE reported daily and evaluated monthly before the subsequent dose escalation  **Secondary Endpoints:**   1. Number of headache-free days per month. 2. Percentage change in average daily pain intensity due to headache on the numeric rating scale (NRS) from baseline to each follow up visit. 3. Sleep, mood and function are to be reported using the percentage change in the scores of PROMIS (patient-reported outcome measurement information system) measures from the Pediatric Item Bank:    1. Pediatric Sleep-related Impairment – Short Form 8a    2. Pediatric Short Form v2.0 - Anxiety - 8a    3. Pediatric Short Form v2.0 - Depressive Symptoms 8a    4. Pediatric Pain Interference – Short Form 8a    5. Pediatric Positive Affect – Short Form 8a    6. Self-directed goal attainment will be reported as a percentage toward a physical, mental and social goal reported by participants at each monthly visit. 4. Family impact scores will be reported by PedsQL™ Family Impact Module, Version 2.0 and compared with baseline scores.   **Exploratory Endpoints:**   1. Steady-state plasma levels of bioactive cannabinoids, namely THC, CBD, 11-OH-THC, 7-OH-CBD, and Cannabichromene, during each follow up visit before dose escalation. 2. Genetic polymorphisms of genes encoding for CYP enzymes and the p-glycoprotein transporter and plasma levels of THC, CBD and their active metabolites in the study participants. |
| Number of Participants | 20 participants |
| Inclusion Criteria | Adolescent patients of the qualified investigator between the ages of 14-17 years with chronic headaches will be enrolled.  They must have headaches (migraine or tension-like features) on more than 15 days per month for more than 3 months and have failed at least two treatment options for either tolerability or efficacy.  Participants must be committed to using contraception, abstaining from recreational cannabis use, and working with psychology and physiotherapy teams as appropriate. |

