| To investigate relationships between the dose-escalation and change in the frequency of headache.  To monitor the effect of CBD-enriched CHE on the intensity of pain related to chronic headache  To evaluate the effect of CBD-enriched CHE on sleep, mood and function in adolescents with chronic headaches.  To explore the impact of chronic headaches on quality of life. | The percentage change in the number of headache-free days per month from baseline to each follow up visit  [Time Frame: monthly throughout the study]  The percentage reduction in the average daily pain intensity due to chronic headache on the Numeric Rating Scale (NRS) from baseline to each follow up visit.  [Time Frame: daily throughout the study]  Sleep, mood, and function are to be reported using the percentage change in the scores of PROMIS  (Patient Reported Outcome Measurement Information System) measures from the pediatric Item bank:   1. Pediatric Sleep-Related Impairment– Short Form 8a scale 2. Pediatric Short Form v2.0 – Anxiety – 8a scale 3. Pediatric Short Form v2.0 – Depressive Symptoms 8a scale 4. Pediatric Pain Interference – Short Form 8a scale 5. Pediatric Positive Affect – Short Form 8a and goal attainment scaling ( participant and parent-reported) 6. Self-directed goal attainment will be reported as percentage toward a physical, mental and social goal reported by participant   [Time Frame: monthly throughout the study]  Scores of PedsQL ™ Family Impact Module Version 2.0 and compared with baseline scores  [Time Frame: monthly throughout the study] | | Headache is a common symptom in patients with chronic headaches; It will be an essential measure to study the effect of CBD-enriched CHE on the incident of headache-free days  It will be helpful to evaluate the effect of CBD –enriched CHE on the intensity of pain related to chronic headache  The pain and discomfort in chronic headaches are associated with the decrease in the quality and quantity of sleep; patients are more likely to suffer from depression and anxiety and have a functional disability, absence of school; these measures will be reasonable to determine the effect of CHE on sleep, mood and physical function  These endpoints will be used to estimate the impact of a CBD- enriched CHE on quality of life. As cannabis products may affect a wide variety of symptoms, including pain, sleep, mood and function, quality of life provides an overall impact on family impact. |
| **Exploratory** **Objectives** | | | |

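### The goal attainment endpoint is defined inconsistently: rating range against top anchor, percentage against a score starting at -2, and participant against participant-and-parent report

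*Protocol*

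**What the plan says.** Four places in the protocol define or use this measure.

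- **Measures of Effectiveness, Goal Attainment Scaling.** The rating rule is that "importance and difficulty are rated on a scale of 4, starting from 0 to 3". The lower label is given as "where 0 means not at all (important/difficult", and the upper label follows as "4 means very important/difficult, leading to the generation of scoring goals". The weighting rule is that "goals are weighted with the importance multiplied by difficulty". Only two attainment levels are described; the sentence starts at minus one (the minus sign falls just before the quoted words): "1 means the patient experiences difficulties in achieving that particular goal, while -2 will be the baseline rate". The reporter is the patient: "Goal attainment scaling is a patient-reported outcome measure".
- **Synopsis, secondary endpoints.** "Self-directed goal attainment will be reported as a percentage toward a physical, mental and social goal reported by participants at each monthly visit".
- **Objectives and Endpoints table.** Item 6 repeats the percentage version, reported by the participant. Item 5, which concerns Positive Affect, also contains "goal attainment scaling ( participant and parent-reported".
- **Baseline Descriptive Statistics (under Statistical Considerations).** Goal attainment scores are among the secondary outcomes to be summarised at each timepoint, with change from baseline in both absolute and percentage terms.

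The Baseline Run-In Phase text adds that each participant picks three goals. The Schedule of Activities collects self-directed goal attainment at all seven visits.

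**The concern.** A reader who tries to compute this endpoint from the protocol cannot tell what is being computed. The rating range and its top label disagree. A percentage of progress and a weighted score anchored at -2 are different quantities, yet both carry the name of the same endpoint. The planned percentage change misbehaves on a negative baseline. Whether a parent's rating enters depends on which item of one table is read.

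The rating range and the reporter are data-collection definitions. If they are wrong on the form, a later analysis plan cannot recover the intended ratings. What is at stake is the interpretability of one secondary measure in 20 participants, not the safety conclusions.

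**Working it through.** The protocol gives no numerical result for this endpoint, so there is no figure to reproduce. The check takes each inconsistency in turn.

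**1. Rating range against top anchor.** Inputs from Goal Attainment Scaling: ratings 0 to 3, top label at 4, weight = importance × difficulty.

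- Top rating 3: largest weight 3 × 3 = 9.
- Top rating 4: largest weight 4 × 4 = 16.

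To see what this does to a score, assume a weighted mean, Σ(w × level) / Σw. The protocol states no scoring formula, so this form and the ratings below are assumptions. Take three goals: one with the top rating on both axes, one rated 2 and 2, one rated 1 and 1. All start at -2, and only the first moves to -1.

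| Top rating | Weights | Follow-up score | Absolute change | Percentage change |
|---|---|---|---|---|
| 3 | 9, 4, 1 | (-9 - 8 - 2) / 14 = -1.36 | 0.64 | 0.64 / (-2) = -32% |
| 4 | 16, 4, 1 | (-16 - 8 - 2) / 21 = -1.24 | 0.76 | 0.76 / (-2) = -38% |

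The two readings differ by 0.12 of a level (0.76 - 0.64).

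**2. Percentage towards a goal against a score starting at -2.** Side by side:

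- Synopsis and endpoint table item 6: a percentage for each of a physical, a mental and a social goal.
- Goal Attainment Scaling: weighted goals, with -2 as the baseline and -1 as the only other level described.

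No passage maps one on to the other.

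**3. Percentage change on a negative baseline.** Percentage change = 100 × (follow-up - baseline) / baseline. For one goal moving from -2 to -1: 100 × (-1 + 2) / (-2) = -50%. Any rise from a negative baseline has a positive numerator and a negative denominator, so every improvement carries a minus sign. The result is not a percentage towards the goal either.

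**4. Reporter.** Endpoint table item 5 names participant and parent. The Synopsis, endpoint table item 6 and Goal Attainment Scaling name only the participant or patient. The table therefore disagrees with itself.

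**5. Secondary point: zero weights.** With 0 allowed on either axis, the product is 0 for 7 of the 16 possible rating pairs on a 0 to 3 range (9 of 25 on 0 to 4). These are counts of possible pairs, not of how often participants would choose them. In the illustration, if the improving goal has weight 0 and the others keep 4 and 1, the score is (0 - 8 - 2) / 5 = -2: the improvement does not appear. If all three weights are 0, the weighted mean is 0/0 and undefined.

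**The case against.** The strongest reply is that this is loose wording with little consequence.

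- **The 4 is probably a slip.** A four-level scale running from 0 to 3 is coherent, and only the later label is off. That is likely, and it makes the correction easy. The text still contradicts itself, and the metric, the sign and the reporter would remain to be settled.
- **The weights of 9 and 16 overstate the effect.** A reader might take 16 against 9 as the size of the error. It is not. A common factor in the weights cancels in a weighted mean: 9, 9, 9 and 16, 16, 16 give the same score. Only the relative weight of top-rated goals changes, which gives the modest shift shown.
- **Sites will not diverge.** A reader might infer that the three centres would score differently and that their data could not be pooled. The protocol does not support that. Data go into a shared REDCap system, with study worksheets provided and automatic range checks (Measures of Effectiveness; Data Collection and Management Responsibilities). What stands is that the protocol does not say which version the form should carry.
- **Zero weight is not a contradiction.** This is correct. It follows from the stated product rule and the 0 label, and giving no weight to a goal rated not at all important is coherent. Three zero-weight goals, all self-chosen, would be unusual. It is less obvious that a goal rated important but not at all difficult should vanish from the score.
- **The parent wording may be misplaced.** It sits in the Positive Affect item, while item 6 agrees with the other passages. It still needs removing or explaining.
- **The analysis plan may supply the formula.** It may, and the absence of a formula or of further attainment levels from the protocol is not counted here. The conflicts listed lie within the protocol's own text.

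**Conclusion.** The point holds, and it is minor. The definition of the goal attainment endpoint conflicts on rating range, metric and reporter, and the planned percentage change gives improvement a negative sign. These rest on the text and on simple arithmetic. The size of the anchor effect (-1.36 against -1.24) rests on an assumed weighted mean and assumed ratings, and it is modest. The zero weight is a weakness of the stated rule, secondary to the contradictions.

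The documents do not support inferring that site data would be unpoolable or that trial conclusions are at risk. This is one component of a secondary endpoint summarised descriptively, in a trial with no prespecified hypothesis. The primary endpoint is adverse events, and neither it nor the sample size of 20 is affected.

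**What to change.** 1. Reconcile the Synopsis, the Objectives and Endpoints table, Goal Attainment Scaling and Baseline Descriptive Statistics to one metric and one reporter.
2. Make the top label agree with the 0 to 3 range, and check the REDCap form against the corrected text.
3. For any score with a baseline of -2, report absolute change only and drop percentage change.
4. Report an unweighted score alongside the weighted one, so that a goal rated 0 on either axis stays visible and a score exists when all three weights are 0.

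The cost is protocol wording, a form check and one extra descriptive summary. No visits or assessments are added.

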**Pediatric Positive Affect – Short Form 8a scale**

The Pediatric Positive Affect item bank is a PROMIS tool used to assess momentary positive or rewarding affective experiences of a child. These experiences consist of feelings and moods, including elation, pride, affection, pleasure, joy, engagement, excitement, happiness, and contentment. The short form of the Pediatric Positive Affect scale is an efficient, accurate, and valid assessment of positive affect in adolescents, and good reliability has been reported. [[131](#_heading=h.2ne53p9)]

**PedsQL™ Family Impact Module**

The pediatric quality of life family impact module aims to measure children’s chronic health conditions on families and parents. The assessments undertaken by the PedsQL are physical, emotional, social, cognitive, worry and communication. The PedsQL scale has demonstrated well-defined validity and reliability. It is the generic tool used to assess the impact of chronic disease in children on their families functioning and health-related quality of life of families. [[132](#_heading=h.12jfdx2)]

**Cannabinoid and metabolite evaluation**

Monthly blood samples will be collected, and routine safety liver and renal lab test will be analysed locally at satellite sites. Dose-exposure-response will compare measurable cannabinoids and active metabolites (e.g., CBD, THC, ∆9-tetrahydrocannibivarin, cannabidivarin, cannabachromene) with changes in adverse events and other secondary endpoints. We will record steady-state minimum plasma concentrations (CSS,min) before each dose escalation and at the end of treatment. Samples will be collected via venipuncture by a registered phlebotomist or research nurse, before participants take the next dose of study intervention. Samples will be sent to [name] lab on dry ice and stored at -70°C, for stability and to avoid cannabinoid substrate binding. Samples for cannabinoid levels will be analyzed in the [name] lab by a validated LC-MS/MS protocol.[116]

**Pharmacogenomic analyses**

Genomic DNA will be extracted from saliva samples using a QIAmp DNA extraction kit in [name] lab. Genotyping will be performed using the Illumina global screening array (GSA) v3 array on the iScan array scanner. The GSAv3 GWAS arrays have been designed to capture both common and rare genetic variation, including all variants that the Clinical Pharmacogenetics Implementation Consortium has shown to affect the function of the selected candidate genes.[[133](#_heading=h.3mj2wkv)] Genotyped variants and samples will undergo standard quality control procedures in PLINK 1.9. [[134](#_heading=h.21od6so)] Imputation of non-genotyped variants will be performed using the Michigan Imputation Server, including the Haplotype Reference Consortium data as a reference, and genetically determined ancestry will be assessed with EIGENSOFT v5. [[135](#_heading=h.gtnh0h)] Association between these variants and response outcomes will be performed using logistic regression.

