# PROTOCOL SUMMARY

## Synopsis

| Title | A Multi-Centre, Tolerability Study of a Cannabidiol-enriched Cannabis Herbal Extract for Chronic Headaches in Adolescents: the CAN-CHA trial |
| --- | --- |
| Short Title | Cannabis for Chronic Headaches in Adolescents (CAN-CHA) |
| Protocol Number | CAN-CHA |
| Version Number | 6.0 |
| Phase | 2 |
| Study Drug | MediPharm Labs MPL-001, CBD:THC 50:2 (50mg of CBD per ml to 2mg of THC per ml, dissolved in medium chain triglycerides oil derived from fractionated palm oil) with a lemon peppermint flavouring 1500mg of total CBD per 30ml bottle |
| Treatment Regimen | MediPharm Labs MPL-001, CBD:THC 50:2, will be used as a study Intervention. Study participants will receive escalating doses of CBD starting at 0.2-0.4 mg/kg/day up to 0.8-1 mg/kg/day followed by a weaning period. Dosed twice a day orally |
| Study Design | A multicenter, open-label, dose-escalation study will be conducted across three centres in Canada to study the safety, tolerability, and effectiveness of a CBD-enriched CHE in adolescents with chronic headaches. The study will consist of four different phases: recruitment, baseline (1 month), treatment (4 months) and weaning (1 month). |
| Study Duration | The participants will be enrolled in the study for 6 months and complete 7 study visits. The overall study is expected to be completed within 24 months.  Recruitment/Screening  Baseline: 1 month, Treatment: 4 months, Weaning: 1 month |
| Objectives | **Primary Objective**: To determine the safety and tolerability of escalating doses of a Cannabidiol (CBD)-enriched Cannabis Herbal Extract (CHE) in adolescents with chronic headaches.  **Secondary Objectives:**   1. To investigate the relationship between the dose-escalation with headache-free days. 2. To monitor the effect of CBD-enriched CHE oil on the intensity of pain related to chronic headaches. 3. To evaluate the effect of CBD-enriched CHE oil on sleep, mood and function in adolescents with chronic headaches. 4. To explore the impact of chronic headaches on quality of life   **Exploratory Objectives:**   1. To investigate the relationship between the dose-escalation and steady-state trough levels of bioactive cannabinoids. 2. To investigate the relationship between pharmacogenetic variations and response outcomes in adolescents receiving CBD-enriched CHE oil. |

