| To investigate the relationship between the dose-escalation and steady-state trough levels of bioactive cannabinoids  To investigate the relationship between pharmacogenetic variation and response outcomes in adolescents receiving CBD-enriched CHE | | Steady-state trough levels of bioactive cannabinoids, namely THC, CBD, 11-OH-THC, 7-OH-CBD, and Cannabichromene during each follow up visit before dose escalation  [Time Frame: monthly throughout the study]    Genetic polymorphisms of genes encoding for CYP enzymes and the p-glycoprotein transporter and plasma levels of THC, CBD and their active metabolites in the study participants | It is an important measure to study the linearity of the pharmacokinetics of the drug product to better understand who responds best and how metabolism changes overtime and between individuals.  Cannabinoid response is highly variable. This will help to get a more clear picture of variability in seen in cannabinoid pharmacokinetic and pharmacodynamic response. |

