### Baseline Descriptive Statistics

The primary statistical analysis will be a descriptive summary of the pattern of incidence and severity of adverse events across dosage levels. Conventional summary statistics will describe baseline characteristics and other outcomes (means, standard deviations, and medians, range and interquartile range (IQR) for numerical variables; counts and percentages for categorical variables). Summaries will be provided both overall and by dosage level. Medians, ranges and IQR, will be provided for the concentrations of CBD, THC and the primary metabolites at each sampling point. The ratio of parent compound concentration to metabolites will also be summarized to explore variability in cannabinoid metabolism. System organ class will present the severity, frequency, and relationship of treatment-emergent AEs to study intervention. The start date, stop date, severity, relationship, expectedness, outcome, and duration of each AE will be reported. Serious treatment-emergent AEs will be presented either in a table or a listing. The secondary outcomes, including pain, sleep impairment, depression, positive affect, anxiety and goal attainment scores, will be summarized at each timepoint; change from baseline will also be reported (both absolute and percentage change).

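### Logistic regression is the only method named for the pharmacogenetic association, but the paired endpoint is continuous plasma levels and no binary response is defined

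*Protocol*

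**What the plan says.** The Pharmacogenomic analyses text, under Measures of Effectiveness, describes saliva DNA, a genotyping array, quality control and imputation. It ends with the only statement of method for this objective: "Association between these variants and response outcomes will be performed using logistic regression".

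The objective is worded in terms of response (Synopsis): "To investigate the relationship between pharmacogenetic variations and response outcomes in adolescents receiving CBD-enriched CHE oil". The Objectives and Endpoints table says the same. The endpoint listed against it in both places is different: "Genetic polymorphisms of genes encoding for CYP enzymes and the p-glycoprotein transporter and plasma levels of THC, CBD and their active metabolites".

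The form of the candidate outcomes is set elsewhere:

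- Plasma levels are trough concentrations, taken repeatedly (Cannabinoid and metabolite evaluation): "We will record steady-state minimum plasma concentrations (CSS,min) before each dose escalation and at the end of treatment".
- The first secondary endpoint in the Synopsis is a count: "Number of headache-free days per month".
- Pain intensity, the PROMIS scales, goal attainment and the family impact module are scores. Baseline Descriptive Statistics summarises the main secondary outcomes as values at each time point and as change from baseline.

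No responder threshold, concentration cut-off or other binary response is defined for this analysis. The planned sample is 20 participants (Sample Size Determination).

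**The concern.** The stated model does not match the type of outcome that the protocol attaches to it. To apply it, someone must first choose a cut-off for each concentration, count or score. That choice is not in the protocol, it could be made after the data are seen, and it throws away part of a small data set.

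The Objectives and Endpoints table justifies this work by the wish to understand how cannabinoid pharmacokinetics and response vary between individuals. That variation is measured on the concentration and score scales, which a binary model discards. With 20 participants and an array chosen to cover rare as well as common variants, carrier counts will often be small, and ordinary logistic regression then tends to break down. At stake is the usefulness of the saliva and monthly plasma samples for this exploratory question.

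**Working it through.** The protocol states no effect size, significance level, allele frequency or response rate for this analysis, so there is no figure of its own to reproduce. Only N = 20 comes from the protocol. Every other input below is an assumption, shown over a range.

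**1. Information kept after dichotomising.** For a normal outcome cut so that a proportion p lies on one side, the information kept about a small shift is φ(z)² / [p(1 − p)], where z is the standard normal quantile at 1 − p.

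| Split | z | φ(z) | Kept | Lost |
|---|---|---|---|---|
| 50/50 | 0 | 0.3989 | 0.3989² / 0.25 = 0.637 | 36% |
| 30/70 | 0.524 | 0.3477 | 0.3477² / 0.21 = 0.576 | 42% |
| 20/80 | 0.842 | 0.2800 | 0.2800² / 0.16 = 0.490 | 51% |

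**2. Chance that the ordinary fit has no finite estimate.** Take one variant coded carrier/non-carrier, no covariates and no genetic effect. The maximum-likelihood estimate is finite only if all four cells of the carrier-by-response table are occupied. With Hardy-Weinberg genotypes the carrier probability is c = 1 − (1 − MAF)². The cell probabilities are c and 1 − c, each multiplied by the response rate r or 1 − r. Inclusion-exclusion then gives the chance of at least one empty cell among 20 participants.

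Example: MAF 0.10, r = 0.5. Here c = 0.19, so 20 × 0.19 = 3.8 carriers are expected. Each carrier cell has probability 0.095, so the chance that a given one is empty is 0.905²⁰ = 0.136. Both are empty with probability 0.81²⁰ = 0.015. The total is 2 × 0.136 − 0.015 ≈ 0.257, because the other terms are negligible.

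| MAF | Carriers expected of 20 | r = 50% | r = 30% | r = 20% |
|---|---|---|---|---|
| 0.05 | 1.95 | 61% | 67% | 75% |
| 0.10 | 3.8 | 26% | 35% | 50% |
| 0.20 | 7.2 | 4% | 12% | 28% |
| 0.30 | 10.2 | 1% | 8% | 23% |
| 0.40 | 12.8 | 4% | 12% | 28% |

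Simulation with 20,000 data sets per setting gives the same values. If only 15 participants were evaluable, the ranges would be 73% to 84% at MAF 0.05 and 41% to 64% at MAF 0.10. Ancestry covariates were not modelled; they would make fitting harder.

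**3. What a real effect does.** With a true carrier shift of 1.5 SD and a median split at N = 20, simulated non-fit is 66% at MAF 0.10, 28% at MAF 0.20 and 16% at MAF 0.30. A strong effect empties cells, so the clearest signals at low-frequency variants are the ones most often left without an estimate.

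**4. Power, for illustration only.** N = 20, MAF 0.20, two-sided 5%, median split where dichotomised, 4,000 simulated data sets per setting:

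| Shift | Continuous (t-test) | Logistic, likelihood ratio | Logistic, Wald | Fisher exact |
|---|---|---|---|---|
| 1.0 SD | 51% | 39% | 21% | 17% |
| 1.5 SD | 84% | 68% | 33% | 40% |

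With carrier numbers fixed and a 10 v 10 split, the smallest attainable two-sided Fisher p is 0.21 with 3 carriers and 0.087 with 4. An exact 5% test on a median split therefore cannot reject with so few carriers, whatever the effect.

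**The case against.** Four points can be made for the plan.

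*Adverse events are a natural binary outcome.* The section on dose-limiting toxicity lists events that stop escalation, which gives a yes/no per participant. The exposure-response text relates cannabinoid levels to "changes in adverse events and other secondary endpoints". Logistic regression is the right type of model for such an outcome. This stands, and it means the method is not wrong for every possible response. But the pharmacogenomic text neither names such an outcome nor limits the method to it.

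*Plasma level is exposure, not response.* The sentence on method speaks of response outcomes, so one could read it as silent on concentrations, with that model left to a statistical analysis plan. The ambiguity is real. It does not remove the mismatch: the endpoint set against the objective is genotype with plasma levels, and the efficacy outcomes that remain are counts and scores without a cut-off. An analysis plan could supply a responder definition, but it would still inherit a binary model for whatever this sentence covers.

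*The analysis is exploratory.* Statistical Hypotheses states that none is prespecified, and the Synopsis declines a power calculation. Power is therefore a secondary yardstick. The loss of information and the missing finite estimates matter for estimation too.

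*A harsher reading goes too far.* A reader might infer that logistic regression discards most of the information, usually cannot be fitted, or has no power. The documents do not support this. A median split keeps 64%, and the loss passes half only near a 20/80 split. Non-fit is rare for common variants with a balanced response. Scenarios with 0% power can be built (4 carriers, 1.5 SD shift, median split, against 72% for a linear model), but they belong to the Wald and Fisher tests under assumed carrier counts, and the protocol names neither test. The likelihood-ratio test from the same model reaches about 64% there, though its type I error is about 8%, so it is not a clean rescue. Firth-penalised or exact methods also avoid infinite estimates.

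**Conclusion.** The point holds in a limited form. The protocol names a binary-outcome model as its only pharmacogenetic method, pairs the objective with a continuous endpoint, lists efficacy outcomes that are counts or scores, and defines no binary response. Dichotomising would lose about 36% to 51% of the information for splits between 50/50 and 20/80, assuming a normal outcome. At N = 20, ordinary maximum-likelihood fits have no finite estimate in 26% to 75% of cases for an MAF of 0.05 to 0.10 and response rates of 50% to 20%, with no genetic effect. Above that frequency the problem is small unless the response is uneven or the effect is strong. No safety, primary or secondary result is affected. The change is worth making because the mismatch is in the text itself and is cheap to remove.

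**What to change.** Replace the closing sentence of Pharmacogenomic analyses with text to this effect:

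- Associations of the candidate-gene variants with log trough concentrations, accounting for dose and for repeated monthly values within a participant, and with changes in headache-free days and scores, will be estimated on their original scale by linear, rank-based or mixed models and reported with 95% confidence intervals.
- Logistic regression, in Firth-penalised or exact form, will be used only for a binary outcome defined in advance, such as occurrence of a dose-limiting toxicity.

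A stated lower limit on MAF or carrier count would also help, since none is given. In the same edit, align the objective (response outcomes) with its endpoint (plasma levels), so that it is clear which outcomes are meant. The cost is a few lines of protocol text, with no added data, visits or participants.
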